### **1.1.5. Regenerative therapy based on autologous MSC**

Regenerative stem cell therapies for a number of conditions are in the first phases of clinical trials. There are about 2,000 listed at [clinicaltrials.gov](http://clinicaltrials.gov) (excluding blood stem cell applications). These first phases test only safety; nonetheless, positive signs are often seen. A recent stem cell trial for blindness (macular degeneration) partially restored the vision of two subjects (Orozco et al., 2011). Pre-clinical data shows numerous potential advantages of regenerative strategies for treatment, such as preservation of normal surrounding anatomy, biomechanics, and motion. Mesenchymal cell therapy has produced exciting results both *in vitro* and *in vivo*. Studies with MSC have been particularly promising (Blanco et al., 2010). In our previous *in vitro* study, the co-culture of human MSC with nucleus pulposus (NP) cells results in upregulation of both NP cell proliferation and activity and MSC differentiation towards the chondrogenic lineage (Vadalà et al., 2008). Recent research indicates that NP contains populations of MSC that are very similar to the MSC recovered from bone marrow (Peng et al., 2013; Hiyama et al., 2008). Beside chondrogenic potential, MSC have shown an anti-inflammatory effect through the release of IL1RA, TSG6, IDO, iNOS, and other anti-inflammatory molecules. MSC are able to inhibit T cell proliferation as well as monocyte activation. This anti-inflammatory effect is important in the benefit observed in IDDD where local inflammation is induced by cartilage degradation. Studies in animal models of disc degeneration have shown that MSC injected in the NP area not only survive for months but also proliferate in canine, porcine and rabbit models (Henriksson et al., 2009; Yang et al., 2010). In addition, transplanted MSC induced production of IVD extracellular matrix proteins, including proteoglycan, aggrecan, and types I and II collagens (Ankrum et al., 2014). Studies from literature were conducted on dogs which underwent a partial nucleotomy at 3 lumbar levels (L3-L4, L4-L5, and L5-L6); adjacent levels served as nonoperated controls. Assessments of the experimental discs plus the 2 adjacent untouched discs were made using MRI, radiography, histology, and biochemistry at 12 months. Disc repair was clearly demonstrated through histology and biochemical analysis: disc injected with MSC more closely resembled the healthy controls as evidenced in matrix translucency, compartmentalization of the annulus, and in cell density within the NP. Matrix analysis for Type-II collagen and aggrecan demonstrated evidence of a better regenerative stimulation to the disc provided by MSC when compared to

controls19c. Finally, these studies also reported that injection of MSC resulted in better preservation of the height and water content of discs (Serigano et al., 2010; Hiyama et al., 2008).

Further proofs of NP regeneration have been obtained by our group in another large size animal study (sheep) conducted by members of the consortium (UCBM). A partial nucleotomy model has been used to test autologous BM-MSC (produced by the Cell Factory) transplantation with cell dose escalation (low or high doses). We have delivered 100µl of the hyaluronan-based hydrogel with a suspension of low or high doses of BM-MSC, using the nucleotomy model without injection as control. We have shown that a high dose of autologous MSC ( $1 \times 10^7$  cell/ml) regenerates the NP IVD in this model with high cell engraftments up to one year after transplantation demonstrated by sequential MRI, gross anatomy evaluation and histology.

Moreover, X-Ray evaluation showed the maintenance of the disc height index (DHI) of the high dose MSC treated group compared to partial nucleotomy control [unpublished data].

More than 450 trials are ongoing in 2016 using allogeneic MSC in regenerative medicine worldwide, with a major focus on cardiovascular pathology, chronic inflammatory diseases, and musculoskeletal pathologies, based on allogeneic cells in most cases (Imran et al., 2015). We propose a large-scale double-blind controlled trial to validate IDDD therapy based on autologous BM-MSC.

## 1.2 Clinical trial rationale

We hypothesize that autologous BM-MSC intradiscal injection in patients affected by LBP due to moderate multilevel lumbar IDD will be able (1) to significantly reduce LBP and improve functional status compared to sham controls. Moreover, the treated IVD will (2) undergo regeneration in terms of MRI changes compared to the sham control group. We also hypothesize that the proposed cell therapy is (3) safe in the long term.

The PI has obtained significant preliminary data in the past 15 years of research activity developing a MSC based therapy for the treatment of IDD. A series of consecutive studies from life science to preclinical tests on large animal models with long follow up have been conducted in order to obtain the data necessary to move toward the clinical translation. *In vitro* long follow up have been conducted in order to obtain the data necessary to move toward the clinical translation. *In vitro* studies of the PI suggested the regenerative potential of MSC results from MSC and NP cells interactions that up-regulate extracellular matrix protein synthesis (Orozco et al., 2011; Blanco et al., 2010). This synergistic effect is due to a combination of MSC differentiation toward NP-like cells and the trophic effect of MSC upon NP cells (Vadalà et al., 2008). The PI also tested the feasibility of the approach in a small animal model (rabbit) with BM-MSC expanded in standard condition showed cell engraftment up to 6 months after transplantation (Blanco et al., 2010). Proof of efficacy has been obtained in a preclinical large animal model (ovine) of IDD (grade IV) developed by the PI (Peng et al., 2013). A dose escalation

study has been conducted to test BM-MSC transplantation within a nucleotomized disc. We have shown that a high dose of autologous BM-MSC ( $1 \times 10^7$  cell/ml) regenerates the NP in a preclinical model of IDD up to one year after transplantation compared to control group. (Fig. 1) [unpublished data].

[figure not shown]

**FIGURA 1A:** L'intensità del segnale del tempo di rilassamento T2, ottenuta dalla RMN del NP e valutata seguendo il grado degenerative secondo Pfirrmann, ha mostrato che i dischi che hanno ricevuto l'iniezione di MSC ad alte dosi appariva di grado II, i dischi con basse dosi di MSC grado III e il gruppo non trattato è apparso come di grado V; **FIGURA 1B:** I dischi trattati con alte dosi di CF-BM-MSC hanno mostrato mantenimento dell'indice RMM rispetto al disco sano e un livello significativo rispetto al controllo negativo.

These recent results have been obtained thanks to a cooperative project coordinated by the PI with the cell factory (Young Investigator Grant of the Italian Ministry of Health, GR-2010-2318448). In the framework of this project Cell Factory have validated the manufacturing process and prepared the Investigational Medicinal Product Dossier (IMPD) containing the quality and non-clinical data on BM-MSC for IVD regeneration.

Indeed, Cell factory is a reliable partner since it has been involved as GMP manufacturing center in several national and international clinical trials. In particular, in the orthopedic field, it provided BM-MSC for a multicentric European clinical trial for bone regeneration in non-union long bone fracture (NCT01842477). In this trial 200 million GMP expanded autologous BM-MSC, combined during surgery with bioceramics, safely obtained bone consolidation in 26 out of 28 patients (92%) with diaphyseal or metaphysodiaphyseal nonunions of femur, tibia or humerus. The PI hold also expertise in conducting RCTs in stem cell therapy. Indeed, the PI at UCBM is currently involved in a multicentric European RCT for disc regeneration. In this project, named RESPINE, allogenic BM-MSC are currently being tested for the treatment of LBP and disc regeneration. UCBM is the solo Italian center involved in the RCT.

### **1.3 Justification of the route administration, dosage and treatment period**

Autologous BM-MSC will be administered via imaging control into the discs affected by IDD where they are expected to exert their therapeutic effects. As we mentioned above, no current standard treatments are available to influence the course of the disease and no drugs/devices brought significant proofs to limit the structural IDD. In the previous studies, a median dose of  $15 \times 10^6$  of MSC was injected with a good outcome and without side effects. Thus, we decided to use a dose of  $15 \times 10^6$  of autologous BM-MSC each disc in the active arm and a sham procedure in the control group without active product.

Several studies have reported that BM-MSC injection is safety, without adverse events [Orozco et al., 2013] [Vega et al., 2015]. Mild adverse reactions, such as pain, have been reported for both groups (sham and treated) without statistically significant differences.

The possibility to treat 3 different discs, each one with the selected dose ( $15 \times 10^6$ ), has been decided according to the results of a recent Phase I clinical study where  $50 \times 10^6$  Adipose derived stem cells were intrarticularly injected without adverse events [Pers et al., 2016].

Based on previous recommended papers, it seems the best option to check efficacy in chronic LBP is a period of more than 6 months. Thus, we retained as primary outcome an improvement of pain and functional status 12 months after treatment.

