## **2.3 Objectives**

### **2.3.1 Primary objective:**

- Evaluate the effectiveness of intradiscal injection of autologous BM-MSCs in reducing chronic LBP due to multilevel (max. 3 levels) lumbar IDD after 24 months of treatment in terms of pain relief (VAS), functionality (ODI) and quality of life (SF36).

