## **2.4 Endpoints**

### **2.4.1 Primary Endpoint:**

- To evaluate the efficacy of intradiscal injection of autologous BM-MSC using the visual analog scale (VAS) and functional status assessed by the Oswestry disability index (ODI) after 24 months of treatment, defining

responders in case of at least 40% improvement in VAS or ODI at month 24 compared to baseline.

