## **4. Measurement of outcomes**

### **4.1 Primary Outcome Measures:**

The clinical response is defined as pain relief of at least 40% and 40 mm decrease on VAS scale between baseline and month 24, or 40% improvement of functional index ODI at month 24 compared to baseline. Chronic LBP is assessed using the VAS pain scale (0 – 100, where 0 represents no pain and 100 represents the worst pain imaginable). ODI scale ranges from 0 to 50 and allows evaluation of disability (0% – 20%: minimal disability; 20% – 40%: moderate disability; 40% – 60%: severe disability; 60% – 80%: crippled; 80% – 100%: bed-bound or exaggerating their symptoms).

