## **7. Statistic analysis planning and power calculation**

Sample size was calculated to have 80% power and 2 balanced groups and according to the literature data (Maher et al., 2017; PopulationReferenceBureau; 2016), a responder rate is expected at 12 months of the order of 30% in controls and 68% for MSC is a delta of 38% between the two groups. To highlight this

difference while justifying a power of 80% and an alpha risk of 5% and within 1:1 ratio, taking into account 20% of inclusion failure, it is necessary to include 26 individuals per group a total of 52 subjects.

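### The primary endpoint is set at month 24, but section 1.3 names month 12 as primary and the 80% power rests only on 12-month responder rates

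*Protocol*

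**What the plan says.** The protocol fixes the primary time point in several places, and they do not agree.

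**Month 12**
- Section 1.3, closing paragraph: "Thus, we retained as primary outcome an improvement of pain and functional status 12 months after treatment".
- Section 7, repeated in the synopsis row on sample size: "a responder rate is expected at 12 months of the order of 30% in controls and 68% for MSC". These rates lead to 26 patients per group, 52 in total.

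**Month 24**
- Section 2.3.1, and the synopsis objective: the effect is to be judged "after 24 months of treatment in terms of pain relief (VAS), functionality (ODI) and quality of life (SF36").
- Section 2.4.1: "responders in case of at least 40% improvement in VAS or ODI at month 24 compared to baseline".
- Section 4.1: response includes "pain relief of at least 40% and 40 mm decrease on VAS scale between baseline and month 24", or an ODI improvement at month 24.

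VAS and ODI are collected at both visits (schedule in 6.1; visit lists in 6.2.9 and 6.2.10). No section is said to take precedence over another. No responder rate for month 24 appears anywhere, and nothing says that the 12-month rates are expected to hold for a further year.

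**The concern.** The time point is part of the definition of a primary endpoint, and the power statement should refer to that endpoint. Here the sentence in 1.3 and the sample-size rates point to month 12, while the sections that define objective, endpoint and outcome point to month 24.

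Two things are at stake. First, the only power figure in the protocol describes month 12. Whether a response lasts through a second year is exactly what a month-24 endpoint tests, so equality of the rates at the two visits is a real assumption and should be declared. Second, as long as 1.3 stands, a later claim on month 12 could cite protocol text in its support.

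**Working it through.** **Inputs.** From section 7: control 30%, MSC 68%, both at 12 months; power 80%, alpha 5%, ratio 1:1; 26 per group. The protocol does not state whether the test is one- or two-sided; two-sided is assumed below, and 26 is taken as the number evaluable.

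**Step 1: reproduce the stated figure.** With pooled variance under the null, p̄ = (p1 + p2)/2 and d = p2 − p1:

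n = [1.960·√(2p̄(1−p̄)) + 0.842·√(p1(1−p1) + p2(1−p2))]² / d²

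- p̄ = 0.49, so 1.960·√0.4998 = 1.386
- √(0.21 + 0.2176) = 0.654, and 0.842 × 0.654 = 0.550
- n = (1.386 + 0.550)² / 0.38² = 25.96, rounded up to 26 per group

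The same 26 also follows from a one-sided 5% test (21 per group) multiplied by 1.2 (25.2, rounded up). On either route the only response rates used are those for month 12.

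**Step 2: power at 26 evaluable per arm.**

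Power = Φ{ [d·√26 − 1.960·√(2p̄(1−p̄))] / √(p1(1−p1) + p2(1−p2)) }

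For 30% vs 68%: (1.938 − 1.386)/0.654 = 0.844, and Φ(0.844) = 80.1%. This is the protocol's 80%, and it refers to month 12.

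**Step 3: month 24.** The documents give no rates, so these are assumptions chosen to move in both directions.

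| Control | MSC | z | Power at 26 per arm | Evaluable per arm for 80% |
|---|---|---|---|---|
| 30% | 68% (12-month rates persist) | 0.844 | 80% | 26 |
| 30% | 60% | 0.225 | 59% | 42 |
| 30% | 55% | −0.141 | 44% | 61 |
| 40% | 68% | 0.068 | 53% | 49 |
| 20% | 68% | 1.744 | 96% | 16 |

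**Step 4: if the ambiguity were exploited.** Suppose whichever visit is significant at two-sided 5% were claimed. For two correlated normal test statistics with no true effect, the error is 1 − P(|Z1| < 1.96 and |Z2| < 1.96): 9.1% at correlation 0.5, 8.3% at 0.7 and 7.0% at 0.9. The correlations are assumed.

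**The case against.** The strongest reply is that month 24 is not really in doubt. Every section whose job is to define the objective or the endpoint says month 24. Only one background sentence, under a heading on route, dosage and treatment period, names month 12 as primary. Section 7 dates an expectation taken from the literature and does not redefine the endpoint. Much of this stands, and it makes the correction easy. It does not remove the sentence in 1.3, and it leaves the power problem where it was: if month 24 is primary, the power calculation is dated to another visit.

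Three stronger readings are tempting, and the documents do not support them.

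- *That the trial has two primary analyses and an inflated error rate.* The protocol nowhere plans to test both visits as primary. The 7–9% arises only if the visit is chosen after seeing results. It also depends on the test, and section 7.1 names only ANOVA and the t test. In a simulation with 26 per arm, a 30% response rate in both arms and latent correlation 0.5–0.9, rejection at either visit was about 9–10% with an uncorrected z test but 4.2–4.7% with Fisher's exact test.
- *That the trial is underpowered at month 24.* Nothing in the document indicates that the MSC response wanes. The control rate could fall as well, and power would then rise.
- *That permitted NSAID use makes month 24 differ from month 12.* Section 6.4 and the footnote to the schedule lift the restriction after the first 6 months, so it is already lifted at month 12. This does not separate the two visits.

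**Conclusion.** The point holds as a contradiction in current text together with a power statement that does not refer to the stated endpoint. Month 24 is the better-supported reading. On that reading the 80% is right only if 30% and 68% also apply at month 24, which the protocol neither states nor justifies.

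The size of the effect on power cannot be fixed from the documents. Over the assumed rates it runs from 44% to 96% at 26 evaluable per arm, assuming a two-sided 5% test and the pooled normal approximation. The risk to the type I error is conditional on misuse that the protocol does not plan, and is secondary to the power mismatch. This should be corrected, because primary time point and power basis are core elements that the protocol itself fixes, and fixes inconsistently.

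**What to change.** - **Sections 2.4.1 and 4.1:** state that month 24 is the only primary time point, and name month 12 as a secondary time point for the responder outcome.
- **Section 1.3:** change the closing sentence to match.
- **Section 7 and synopsis:** either give planning rates for month 24 with their source, or state openly that the 12-month rates are carried forward. In both cases state the sidedness and show power over a range in both directions, such as the one tabulated above.

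The cost is wording in a few sections and one short table. No visit or assessment changes. Removing the contradiction does not in itself require a different sample size. The stated power may look less favourable, however, and if the sponsor's own month-24 rates fall short of a 38-point difference, the sample size may have to be reconsidered.

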## 1.4 Risks

A large number of trials have risen rapidly investigating the efficacy in treating conditions such as type I and II diabetes, liver cirrhosis and regeneration, fistulas, cardiovascular disease (ClinicalTrials.gov Identifier NCT00999115), limb ischemia, amyotrophic lateral sclerosis and lipodystrophy (<http://clinicaltrials.gov>). More than 400 trials have been conducted with more than 1000 patients treated with MSC. Furthermore, BM-MSC are also under examination in clinical case studies for graft-versus-host disease immunosuppression, rheumatoid arthritis, Crohn's disease and ulcerous colitis, multiple sclerosis, soft tissue augmentation and bone tissue repair (Fang et al., 2006; Fang et al., 2007) with a clinical benefit, as well as appropriated tolerance. Clinical experience is available with both autologous and allogeneic BM-MSC administration.

- Systemic effects: The autologous nature of the study medication effectively excludes the risks of transmission of infectious agents, graft rejection, or GVHD (Graft versus host disease). The risk of systemic infection, bacteraemia, or sepsis due to contamination of the cell preparation is negligible. .
- Local effects: the complications are the same as in the discography, and rarely presented. The most common complaint is the exacerbation of pain for 1-2 weeks, which is usually solved by analgesia and muscle relaxants for a short period. The most serious complication is discitis, occurring in less than 0.1 % (Osti et al., 1990). Procedure related adverse events such as of infections, bleedings, nerve irritations and nerve injuries with its possible consequences paresthesia and paralysis are exceptional during the injection using the CT scan or fluoroscopic guidance, but patients will be informed.

## 1.5 Benefits

The objective of this clinical trial is to generate efficacy and tolerability profiles of a single injection of  $15 \times 10^6$  cell/ml each of autologous BM-MSC for each disc affected by IDD (up to 3 discs) versus sham procedure. The affected discs (max 3) are treated simultaneously once only, at the V0 visit and no subsequent doses are expected.

The potential of BM-MSC to lead to a disease-modifying therapeutic option for the treatment of this chronic and debilitating disease will be assessed by MRI after 6 months, 1 and 2 years.

## 1.6 Risk-benefit assessment

This study will progress beyond the current state of the art as it will be the one of the first clinical trial to reach significance in assessing autologous BM-MSC for the treatment of IDD. This study provides the first major step in determining subsequent clinical and commercial activity relating to stem cell therapy. It will definitively

provide robust in patient regenerative medicine research that either supports or refutes the potential of intradiscal injection of BM-MSC for the treatment of LBP due to IDD grade 3-4 modified Pfirrmann and grade 3-7 Griffith grading system at different levels (max. 3 levels). If successful, this will allow a new therapy to be taken to the next level of testing, taking the field closer to marketability and delivery, a key step that has eluded stem cell therapies to date.

Based on previous clinical experience with similar products reported in the literature, BM-MSC is deemed to be effective and safe in various diseases. Manufacturing of the study medication is performed according to GMP standards. The risk of local or systemic infection, bacteremia, or sepsis due to contamination of the cell preparation seems negligible. Pre-clinical *in vitro* and *in vivo* evaluations of the study medication did not show any hint of tumorigenic potential of the preparation or systemic migration of BM-MSC after intra-discal injection. There is a low risk of systemic AEs occurring after the end of the observation period, but the sample size of this clinical trial implies a very low probability of detecting rare events anyway. At last, procedure related adverse events such as of infections, bleedings, nerve irritations and nerve injuries with its possible consequences paresthesia and paralysis are very rare as the injection are performed using the fluoroscopy to guide the surgeon, but patients will be informed.

The benefit for patients with chronic LBP may be considerable, since BM-MSC might represent the first disease-modifying therapeutic option for this chronic and debilitating disease. Furthermore, under certain pre-defined conditions, e.g. the occurrence of suspected unexpected serious adverse reactions (SUSARs), the Sponsor will suspend treatment of subjects until a decision whether to continue the clinical trial or not has been taken. In conclusion, subjects will be exposed to limited risks during their participation in this clinical trial.

Therefore, the risk-benefit ratio for this clinical trial is anticipated to be favourable and advocates its conduct in the selected group of subjects. Members of the a pilot trial demonstrating the feasibility and safety of the procedure has been already carried out. The currently proposed trial would be performed by experienced researchers who have already tested cell therapy materials and protocols with the following characteristics.

